### Sample size

It is planned that 134 patients with progressive MA-ILD will be randomised. In the INBUILD trial in patients with progressive pulmonary fibrosis, the mean (SD) change (increase) from baseline in the L-PF questionnaire dyspnoea domain score at week 12 was 0.59 (13.44) in the nintedanib group and 1.45 (13.04) in the placebo group. Assuming that 134 patients are enrolled in MINT and the drop-out rate is 20%, 108 patients (54 in each treatment group) will have complete follow-up data at week 12. With 108 patients, and assuming a standard deviation of 13.44, the width of a 2-sided 95% confidence interval for the between-group difference in the change in L-PF questionnaire dyspnoea domain score at week 12 in MINT is 2.54, which is considered appropriate for an exploratory study.

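### The stated 95% CI width of 2.54 for the between-group difference is wrong: 54 per group with SD 13.44 gives about ±5.1, a full width of about 10.1

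*Protocol article*

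**What the plan says.** All of the relevant text is in the Sample size section of the protocol article.

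- Patients randomised: "It is planned that 134 patients with progressive MA-ILD will be randomised".
- After an assumed 20% drop-out: "108 patients (54 in each treatment group) will have complete follow-up data at week 12".
- Source of the SD: the mean (SD) week-12 change in the L-PF dyspnoea score in the INBUILD trial "was 0.59 (13.44) in the nintedanib group and 1.45 (13.04) in the placebo group". The larger of the two SDs is carried forward.
- Precision: "With 108 patients, and assuming a standard deviation of 13.44, the width of a 2-sided 95% confidence interval for the between-group difference" is followed by the statement that this "change in L-PF questionnaire dyspnoea domain score at week 12 in MINT is 2.54, which is considered appropriate for an exploratory study".

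The article gives no power calculation, target difference or other ground for the sample size. The Analyses section plans descriptive summaries without inferential statistics, and the Discussion lists the relatively small sample among the limitations.

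**The concern.** An interval 2.54 points wide for a difference between two groups of 54, on a scale with SD 13.44, is too narrow on sight. One group mean of 54 already has a standard error of 13.44/√54 = 1.83, and a difference of two such means has a larger one.

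The figure matters because it is the only quantitative property claimed for the design. The plan has no hypothesis test and no power statement, so precision carries the whole argument for the sample size, and the article's judgement of adequacy attaches directly to 2.54. A reader who takes the figure at face value expects the week-12 difference to be known to within about ±1.3 points. If the real margin is four times that, an estimate near zero could be taken as stronger evidence of no benefit than the data can supply.

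**Working it through.** **Inputs, all from the Sample size section except the allocation ratio (Study design and participants):**

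- n = 54 per group with week-12 data, 1:1 allocation
- SD = 13.44 for the change score
- two-sided 95% interval for the between-group difference
- stated width 2.54

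**Drop-out step.** 134 × 0.8 = 107.2, or 53.6 per group. Rounding up gives 54 per group and 108 in total. This agrees with the article.

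**Attempt to reproduce 2.54 as the quantity named.**

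SE of the difference = SD × √(1/54 + 1/54) = 13.44 × √(2/54) = 2.587

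Half-width = 1.96 × 2.587 = 5.07

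Full width = 2 × 5.07 = 10.14

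With the t quantile on 106 degrees of freedom, the half-width is 5.13 and the full width 10.26. The stated figure is not reproduced: 2.54/10.14 = 0.25 of the width, and 2.54/5.07 = 0.50 of the half-width.

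**Other readings of the two-group interval:**

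| Reading | Half-width | Full width |
|---|---|---|
| 54 per group, SD 13.44, z | 5.07 | 10.14 |
| 54 per group, SD 13.44, t | 5.13 | 10.26 |
| 54 per group, SDs 13.44 and 13.04, z | 5.00 | 9.99 |
| 67 per group (no drop-out), z | 4.55 | 9.10 |
| 108 per group, z | 3.59 | 7.17 |
| 54 per group, 90% level, z | 4.25 | 8.51 |
| 54 per group, 80% level, z | 3.32 | 6.63 |

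None gives 2.54 in either column.

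**What 2.54 would require:**

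- As a full width: n = 2 × (1.96 × 13.44/1.27)² ≈ 860.4, so 861 completers per group.
- As a half-width: n = 2 × (1.96 × 13.44/2.54)² ≈ 215.1, so 216 per group.
- With 54 per group, the SD would have to be 3.37 (full width) or 6.73 (half-width), against the stated 13.44.

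**Possible origin.** The half-width for a single mean with all completers pooled is 1.96 × 13.44/√108 = 2.535, and with the unrounded 107.2 completers it is 2.544. The figure may therefore be a one-sample margin of error. It is also near one standard error of the difference (2.587, or 2.548 with the two separate SDs). The origin is an inference, and the finding does not depend on it.

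**Scale.** The INBUILD means in the same paragraph differ by 1.45 − 0.59 = 0.86 points. The half-width of 5.07 is 5.07/0.86 = 5.9 times that. If the true difference were 0.86, the estimate would have the wrong sign with probability Φ(−0.86/2.587) = 0.37.

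**The case against.** No reading of the text makes 2.54 correct. What can be argued is how much the error matters.

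- **The trial is exploratory.** No test, decision rule or success criterion uses the figure, and the article concedes a small sample and the lack of planned testing. This is true and limits the harm. It does not correct the number: with no test planned, precision is the only design claim there is. An exploratory aim may well justify accepting ±5.1, but that judgement has to be made on ±5.1.
- **Covariate adjustment could narrow the interval.** The paragraph mentions none. The adjustment would need a correlation of about 0.87 with the change score to bring the half-width to 2.54, and about 0.97 to bring the full width there.
- **The full protocol or analysis plan may give the correct figure or further grounds.** That is possible, as neither is shown. The published statement would still be wrong.
- **The article does not adopt 0.86 as a target.** This stands. The comparison with 0.86 and the 37% wrong-sign probability show scale only and are not part of the error.
- **Misreading by readers is a prediction.** This also stands. A confidence-interval half-width is not a detectable difference and should not be presented as one.

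**Conclusion.** The figure is wrong as written. On the article's own inputs, the 95% interval for the week-12 difference in L-PF dyspnoea score is about ±5.1 points, with a full width of about 10.1. The article overstates precision four-fold as a width, or two-fold if a half-width was meant.

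The result assumes an unadjusted comparison of two independent groups of 54 with a common SD of 13.44, as the paragraph states. Using both INBUILD SDs or the t quantile moves the full width only between 9.99 and 10.26. The cause of the error cannot be established from the text. That precision is the sole justification for the sample size is a statement about this article, since the full protocol is not at hand.

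**What to change.** Replace the precision sentence with wording such as:

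*With 54 patients per group and a standard deviation of 13.44, the two-sided 95% confidence interval for the difference between groups is expected to extend about 5.1 points either side of the estimate (full width about 10.1).*

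Then state whether that precision is acceptable for the trial's exploratory purpose, and why. The correction does not in itself call for a different sample size. Whether the present number remains adequate is for the sponsor to say against the correct figure. The same sentence in the full protocol and analysis plan should be checked and amended if it carries 2.54.

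A short statement that an interval including zero will not be read as showing no effect would help, but it is optional and secondary to the numerical correction.

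The cost is one sentence, plus a published correction to the article. The endpoint, randomisation and planned analysis are unaffected. The stated precision becomes less favourable.

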### Analyses

Descriptive statistics will be used to summarise the results in each treatment group. No inferential statistics will be performed given the exploratory nature of the study. Efficacy analyses will be performed following an intention-to-treat strategy. Except for safety and tolerability, endpoints at weeks 12 and 24 will be evaluated in patients who have ≥ 1 measurement for the endpoint within the relevant time-frame. Safety and tolerability will be evaluated in patients who receive ≥ 1 dose of trial drug.

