## Methods/design

### Study design and participants

MINT is an exploratory, multi-centre, prospective, randomised, double blind, placebo-controlled trial. Eligible patients will be randomised 1:1 to receive nintedanib 150 mg twice daily (bid) or placebo stratified by local vs decentralised site and by use of immunosuppressive therapy (mycophenolate mofetil vs others). Patients will receive blinded treatment for 12 weeks, after which all patients will receive open-label nintedanib for 12 weeks (Fig. 1). Treatment interruptions for ≤ 4 weeks and dose reductions to 100 mg bid will be allowed to manage adverse events. Specific recommendations will be provided to the investigators for the management of diarrhoea and hepatic enzyme elevations (Additional file 1). Patients who prematurely discontinue trial medication will be asked to complete all scheduled visits.

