**Challenges**
A level of digital literacy is required
Participants may feel overburdened with the devices they need to use at home
Additional infrastructure, training and IT support are required
Some patients prefer face-to-face clinical contact

Strengths of MINT include its randomised placebo-controlled design, the enrolment of patients taking standard of care immunosuppressive therapy, the choice of a patient-reported outcome as a primary endpoint, the collection of data on a wide range of endpoints, the use of both local sites and a decentralised site and the mostly remote conduct of the trial. Limitations include a relatively small sample size, short trial duration, and lack of pre-specified statistical testing.

In conclusion, MINT is an innovative hybrid trial that will evaluate the effects of nintedanib on symptoms, quality of life, and ILD progression in patients with progressive MA-ILD and provide valuable information on the utility of decentralised recruitment and remote data collection in clinical trials.

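### The trial is sized on a 95% CI for the between-group difference, but the Analyses section, read literally, excludes that interval

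*Protocol article*

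**What the plan says.** In the protocol article, the Sample size section gives no power calculation. It rests the planned number on "the width of a 2-sided 95% confidence interval for the between-group difference" in the primary endpoint, puts that width at 2.54 points, and judges it acceptable for exploratory work.

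The Analyses section takes a different line: "Descriptive statistics will be used to summarise the results in each treatment group", followed directly by "No inferential statistics will be performed given the exploratory nature of the study". It names no between-group estimate and no interval.

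Two statements in the Discussion bear on how to read this. The conclusion says that the trial will "evaluate the effects of nintedanib on symptoms, quality of life, and ILD progression in patients with progressive MA-ILD". The limitations, just before it, list the absence of pre-planned tests. They do not list an absence of estimation.

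**The concern.** The effect of nintedanib in a blinded, placebo-controlled randomised trial is a contrast between arms. The Sample size section treats the interval around that contrast as the trial's main product, while the Analyses section, taken at its word, rules the interval out. An analysis plan that reports the interval would depart from the published statement. One that follows the statement would leave the sample size justified by a quantity that is not produced.

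The reason given for the exclusion does not support it. Exploratory status is a good reason to avoid confirmatory tests and claims based on p-values. It is no reason to omit an estimate with its uncertainty, and the Sample size section itself treats an interval as compatible with an exploratory study.

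Two things are at stake. If the wording stands, the choice to show an interval could be made after the data are seen. And the only published guide to precision would be the figure of 2.54, which the stated inputs do not support.

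**Working it through.** **Comparing the sections**

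| Place in the protocol article | Quantity | Status |
|---|---|---|
| Sample size | 95% CI for the between-group difference, week 12 | Sole basis for the number of patients |
| Analyses | Summaries within each arm | Planned |
| Analyses | Inferential statistics | Excluded without qualification |
| Discussion, limitations | Statistical tests | Not pre-specified |

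The first and third rows cannot both hold literally, because a confidence interval for a difference is inferential. The first and fourth rows can: a plan may have no tests and still report estimates with intervals. The Analyses sentence is therefore wider than the authors' own account of the limit.

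**What the interval would look like**

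Inputs, all from the Sample size section except the 1:1 allocation (Study design and participants):
- 134 randomised, drop-out 20%, and "108 patients (54 in each treatment group) will have complete follow-up data at week 12"
- SD 13.44
- INBUILD week-12 mean (SD) changes of 0.59 (13.44) on nintedanib and 1.45 (13.04) on placebo

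*Drop-out.* 134 × 0.80 = 107.2, and 108 / 0.80 = 135. The step from 134 to 108 is consistent to within rounding.

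*Stated width of 2.54.* For a difference between two means:
- SE = 13.44 × √(1/54 + 1/54) = 2.59
- Half-width = 1.96 × 2.587 = 5.07 (normal), or 5.13 (t, 106 df)
- Full width = 10.14 (normal), or 10.26 (t)

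Using both INBUILD SDs gives SE = √(13.44²/54 + 13.04²/54) = 2.55, half-width 4.99 and full width 9.99. The stated 2.54 is not reproduced as a full width or a half-width of a between-group interval. A single-mean half-width with all 108 patients comes close, 1.96 × 13.44 / √108 = 2.53, but that is not an interval for a difference. The article does not show how its figure was obtained.

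*Completers needed for 2.54.*
- As a half-width: 2 × (1.96 × 13.44 / 2.54)² = 215.1, so 216 per group
- As a full width: 2 × (1.96 × 13.44 / 1.27)² = 860.4, so 861 per group

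*Illustration.* If the INBUILD difference were observed exactly, 0.59 − 1.45 = −0.86, the interval would be −0.86 ± 5.13, or about −5.99 to 4.27.

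**The case against.** The strongest reply is that the Analyses sentence means only that no hypothesis tests are planned. The limitations paragraph supports this, and so does the use of a confidence interval for sizing. The section does not say that arm summaries are all that will be shown, and a raw difference in means is itself descriptive. The article is also a condensed account: the full protocol and analysis plan are not at hand, and the layout of results is commonly left to them.

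Most of this stands, and it limits what can be claimed. A reader might infer that the treatment effect and its uncertainty would never be reported. The documents do not say so. A reader might also infer that descriptive output would hide the imprecision. It need not: n, mean and SD by arm, the form in which the article quotes INBUILD, are enough to derive the SE, as the calculation here does.

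It is also tempting to size the point by noting that, with no true effect, the arm means would differ by more than one SE in about 32% of trials. That holds for any approximately normal estimate under any analysis plan, so it says nothing about this wording.

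What does not stand is treating the matter as detail left to another document. The article makes a positive, unqualified exclusion that conflicts with its own basis for sizing.

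**Conclusion.** The contradiction is real, but it is one of wording. As written, the Analyses section does not provide for, and read literally excludes, the interval on which the trial was sized. The conflict itself rests on no calculation, only on a confidence interval counting as an inferential statistic. Nothing shows that the sponsor intends to withhold the difference or its interval, and randomisation, blinding, endpoints and data collection are unaffected. It merits correction because it concerns the primary endpoint.

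The related numerical point is firmer. With 54 per group, SD 13.44 and an unadjusted comparison of means, the interval is about ±5.1 points, so its full width is about four times the stated 2.54. Restoring the interval without correcting that figure would leave readers expecting far more precision than the trial can give.

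**What to change.** Replace the sentence that excludes inferential statistics with:

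*No confirmatory hypothesis tests are planned. For the primary endpoint, and for key secondary endpoints at week 12, the between-group difference (nintedanib minus placebo) will be reported with a two-sided 95% CI, interpreted as estimation without multiplicity adjustment. Week-24 results, obtained after both arms receive open-label nintedanib, will be presented as such.*

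The week-24 clause is needed because several key secondary endpoints are also measured then, when the arms no longer compare nintedanib with placebo.

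Alongside it, correct the Sample size section to state an expected SE of about 2.59 and a CI of about ±5.1 points (full width about 10.1 to 10.3) with 54 per group and SD 13.44, and reconsider whether that precision is still judged acceptable.

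The cost is one replacement passage, one corrected figure and negligible programming. The planned number and trial conduct do not change. Make the change before unblinding, so that the choice to report the interval cannot depend on the results.

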### Endpoints

Patients will complete the L-PF questionnaire [30] at baseline and then every 4 weeks. This questionnaire, which was developed in patients with pulmonary fibrosis [31], includes a symptoms module (23 questions with recall of the past 24 h) and an impacts module (21 questions with recall of the past week). The symptoms module includes three domains: dyspnoea, cough, fatigue. The primary endpoint in MINT is the change in L-PF questionnaire dyspnoea domain score at week 12.

Key secondary endpoints include the change in L-PF questionnaire dyspnoea domain score at week 24; changes in L-PF questionnaire cough domain, fatigue domain, impacts, and total scores at weeks 12 and 24; the proportion of patients with an increase in dose or change in glucocorticoid/immunosuppressive agent at weeks 12 and 24; and changes in lung function based on clinic PFTs at weeks 12 and 24 (Additional file 2). Safety and tolerability will be evaluated through assessment of adverse events and the proportion of patients who discontinue trial medication.

The rates of patient recruitment, enrolment, screen failure, and drop-out at the local sites and decentralised site will be evaluated. Data collected using remote and clinic enrolment will be compared. The measurement properties of home spirometry versus clinic spirometry will be assessed. Other secondary and exploratory endpoints, including changes in physical activity, steroid use, semi-quantitative and quantitative HRCT scores, pulse oximetry, patient-reported outcomes, and progression-free survival are shown in Additional file 2.

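### Efficacy is labelled intention-to-treat, but the stated rule is an available-case set with an undefined time-frame, which may bias the week-12 comparison

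*Protocol article*

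**What the plan says.** Two consecutive statements in the Analyses section of the protocol article set the efficacy population. The first is the principle: "Efficacy analyses will be performed following an intention-to-treat strategy". The second is the rule: "Except for safety and tolerability, endpoints at weeks 12 and 24 will be evaluated in patients who have" at least one "measurement for the endpoint within the relevant time-frame". The article does not say what the time-frame is.

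Three other places bear on it:

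- **Sample size.** "It is planned that 134 patients with progressive MA-ILD will be randomised", and with a 20% drop-out allowance "108 patients (54 in each treatment group) will have complete follow-up data at week 12".
- **Endpoints.** "Patients will complete the L-PF questionnaire [30] at baseline and then every 4 weeks". Scores are therefore scheduled at weeks 4 and 8 before the primary time point.
- **Study design and participants.** Allocation is 1:1, and patients who stop trial drug are asked to stay on the visit schedule.

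The Analyses section also says that results are descriptive, with no inferential statistics.

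**The concern.** Intention-to-treat means that every randomised patient counts in the arm assigned. A set defined by having a post-randomisation measurement does not do that. Membership depends on something that happens after randomisation and may differ between arms, and each endpoint can have its own set.

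The undefined time-frame leaves two readings, and neither gives a clean week-12 comparison of all randomised patients:

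- **Week-12 visit window.** Patients without a week-12 score leave the primary comparison, and the week-4 and week-8 scores that many of them gave are not used.
- **Any value from baseline to week 12.** Patients with an earlier score stay in, but a week-4 or week-8 score may then enter a summary labelled week 12.

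Because the trial plans no tests, the arm summaries are the efficacy result. Selective loss distorts a descriptive mean as much as a test statistic. The difference that the article takes from INBUILD is under one point, so a small distortion matters for interpretation.

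**Working it through.** **Step 1: the plan's own figure.** Inputs from the Sample size section are 134 randomised and 20% drop-out. 134 × 0.80 = 107.2, or 53.6 per arm, rounded up to 54. The stated 108 reproduces. The expected shortfall is 134 − 108 = 26 patients, 13 per arm, and 26/134 = 19.4%.

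**Step 2: how many leave.** Under the week-12-window reading, up to about 26. Under the any-value reading, fewer. The article does not allow the second number to be computed.

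**Step 3: reference effect.** Mean changes of 0.59 (nintedanib) and 1.45 (placebo) in the Sample size section give 0.59 − 1.45 = −0.86. I take a higher score as worse, so a negative bias flatters nintedanib.

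**Step 4: bias formula.** In each arm let m be the share missing and g the mean week-12 change of missing patients minus that of observed patients. The mean over all randomised patients is the observed mean plus m × g. Hence

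bias of the observed-case difference = −(mN × gN − mP × gP).

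The article gives neither m by arm nor g, so all values below are assumptions. A useful scale is the gap that, in one arm only at 20% missing, produces a bias equal to the reference effect: 0.86/0.20 = 4.3 points.

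| Missing N / P | Gap N / P | Calculation | Bias |
|---|---|---|---|
| 20% / 20% | 4.3 / 4.3 | −(0.86 − 0.86) | 0 |
| 25% / 15% | 4.3 / 4.3 | −(1.075 − 0.645) | −0.43 |
| 30% / 10% | 4.3 / 4.3 | −(1.29 − 0.43) | −0.86 |
| 25% / 15% | 0 / 4.3 | −(0 − 0.645) | +0.65 |
| 20% / 20% | 0 / 4.3 | −(0 − 0.86) | +0.86 |
| 15% / 25% | 0 / 4.3 | −(0 − 1.075) | +1.08 |

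These rows span about −0.9 to +1.1. That is an illustration, not a bound. The mirror image of the last row gives −1.08, and a gap of 10 points in the nintedanib arm alone at 20% missing gives −2.0.

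**Step 5: cross-check by simulation.** Assumptions: 67 per arm, SD of change 13.44, correlation 0.7 between visits, log-odds of drop-out rising by 0.06 per point of week-8 worsening, 4,000 trials.

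- Drop-out 25%/15%, same dependence in both arms: about −0.45. This implies a gap of 0.45/0.10 = 4.5 points, so 4.3 is not extreme in this set-up.
- Drop-out 30%/10%, same dependence: about −0.85 to −0.9.
- Drop-out 25%/15%, related to dyspnoea on placebo only: about +0.7 to +0.8.
- Drop-out 20%/20%, same dependence, or 25%/15% unrelated to dyspnoea: about 0.
- An estimate over all randomised patients using baseline, week-4 and week-8 scores: about 0 in each of these cases.

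**The case against.** **Much of this belongs to the SAP.** Visit windows and missing-data methods are commonly left there, and this is a condensed article. That stands, and the absence of a missing-data method is not part of the point. What remains is a rule that the article does state and that does not match the label beside it. A SAP that follows the article would carry the mismatch forward.

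**Part of intention-to-treat is kept.** Nothing departs from analysis by assigned arm, and patients who stop drug are asked to continue visits, most of them remote. An adverse event that ends treatment therefore need not cost an L-PF score. This stands too. It may make the loss smaller than 20%, but it does not bring back patients without a measurement.

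**The effect is small beside the noise.** With 54 per arm, the standard error of the difference is 13.44 × √(2/54) = 2.59, so a bias of 0.86 is about a third of it. (The interval width of 2.54 in the Sample size section does not fit this formula. That is a separate matter.) The comparison is fair, but a reported mean difference or interval gives no sign that it has been shifted.

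A reader might infer several stronger things that the documents do not support:

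- *That 20% of patients are certain to be dropped.* This holds only under the week-12-window reading. The 20% is a planning allowance for complete follow-up, with no split by arm.
- *That the comparison is biased in favour of nintedanib.* The sign follows from the assumed pattern. If nintedanib patients leave for tolerability and placebo patients for worsening dyspnoea, it points against nintedanib. If loss is alike in both arms, the bias is zero.
- *That earlier scores will be carried forward.* No such method is named.
- *That bringing back missing patients yields a large gain in precision.* In simulation the standard error fell from 2.62 (unadjusted, observed) to 2.46 with baseline adjustment of observed cases alone, and to 2.40 with the all-randomised method. Most of the gain is baseline adjustment.

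**Conclusion.** The point holds as a mismatch between label and rule, with a possible bias of unknown sign. The stated set is available-case and may vary by endpoint. On the article's own figures up to about 26 of 134 patients (19%) could be outside the primary comparison if the time-frame is the week-12 window. Under the assumed patterns the bias is about −0.9 to +1.1 points, and it is 0 when the share lost and the gap are the same in both arms. The reference difference is 0.86.

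These sizes rest on drop-out splits, gaps and correlations that appear nowhere in the article. That the all-randomised estimate removed the bias also has a limit: in the simulations drop-out depended only on a week-8 score that was always observed, so the missing-at-random assumption held by construction.

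This should be corrected before analysis because the remedy is cheap and uses data already scheduled. It does not undermine the trial.

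**What to change.** In the Analyses section, or in the SAP with a matching correction of the label:

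1. Define the time-frame for the primary endpoint as the week-12 visit window, and give its limits.
2. Estimate the week-12 difference in L-PF dyspnoea change, with a 95% confidence interval, in all randomised patients as assigned. Use all scores at baseline and weeks 4, 8 and 12, including those after stopping trial drug, in a baseline-adjusted repeated-measures model. No hypothesis test is needed. The Sample size section already justifies the trial by the precision of this difference, so reporting an estimate with its interval fits the exploratory aim.
3. Keep the observed-case descriptive summary as secondary, and call it available-case rather than intention-to-treat. Show the number contributing by arm for each endpoint.
4. Add one sensitivity analysis that assigns worse values to patients missing at week 12, including deaths.

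The cost is a few sentences and modest programming. The main estimate then relies on a missing-at-random assumption, which item 4 probes. No new data, visits or patients are required.
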